### 8.4 analyses

Primary endpoints: The proportion of participants in the intervention group who attended at least one appointment with the link worker and the proportion of participants who discontinued the study before the 6-month follow-up (dropout rate) will be analyzed descriptively, with frequencies and percentages, including 95% confidence intervals per treatment group. The comparison of the dropout rate between the treatment groups will be done descriptively and using logistic regression to determine possible influencing factors.

Secondary endpoints are analyzed descriptively (frequencies/percentages, mean/standard deviation or median/interquartile depending on scale and distribution, each with corresponding 95% confidence intervals).

Comparisons between treatment groups will be performed using logistic regression (binary endpoints) or analysis of covariance (continuous endpoints adjusted for baseline , if available), taking center into account.

Safety: Adverse events are analyzed descriptively (frequencies and percentages per treatment group).

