| Comparison of Social Prescription
vs. TAU+ in Health Economic
Endpoints                                       | Subjective health status (3-month follow-up and 6-
month follow-up compared to baseline)                                                                                                                                                                                                                             |
|                                                                                                                     | Utilization behavior of health-related services, in
particular the domains: hospital stays and inpatient
care facilities, emergency care, outpatient health
services and social services, medication, informal
care, incapacity for work (3-month follow-up and 6-
month follow-up compared to baseline) |

|                                  |                                   |                                                                                                             |                 |
|----------------------------------|-----------------------------------|-------------------------------------------------------------------------------------------------------------|-----------------|
| Version: V1.2                    | Last review:
February 12, 2025 | Created: [name], [name], [name], [name], [name] | Page
18of 52 |
|                                  |                                   | Reviewed by: [name], [name]                                                        |                 |
| Release on:
February 12, 2025 | Next check:
N/A                | Released: [name]                                                                           |                 |
|                                  |                                   | Valid from: 04.09.2024                                                                                      |                 |

|                |                          |                                                              |  |
|----------------|--------------------------|--------------------------------------------------------------|--|
| study protocol | Study: „Soziales Rezept“ | Campus:
CCM                                               |  |

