| survey instruments                  |                              |                               |                           |                                                       |                   |                   |
| feasibility endpoints                      | X                            | X                             | X                         | X                                                     | X                 | X                 |
| WHODAS 2.0                                 |                              | X                             |                           |                                                       | X                 | X                 |
| WHO-5                                      |                              | X                             |                           |                                                       | X                 | X                 |
| L-1                                        |                              | X                             |                           |                                                       | X                 | X                 |
| ICECAP-A                                   |                              | X                             |                           |                                                       | X                 | X                 |
| EQ-5D-5L                                   |                              | X                             |                           |                                                       | X                 | X                 |
| De Jong Gierveld Loneliness Scale          |                              | X                             |                           |                                                       | X                 | X                 |
| Target-based endpoint (intervention arm)   |                              |                               | X                         |                                                       | X                 | X                 |
| utilization behavior (PECUNIA-RUM)         |                              | X                             |                           |                                                       | X                 | X                 |

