### 8.5 sensitivity analyses

Relevant endpoints will additionally be analyzed using the per-protocol population.

Subgroup analyses are carried out for relevant endpoints. The following subgroups are used, among others:

- Gender
- underlying psychosocial problem(s)
- age groups.

|                                  |                                   |                                                                                                         |                  |
|----------------------------------|-----------------------------------|---------------------------------------------------------------------------------------------------------|------------------|
| Version: V1.2                    | Last review:
February 12, 2025 | Created: [name], [name], [name], [name], [name] | Page
34 of 52 |
|                                  |                                   | Reviewed by: [name], [name]                                                    |                  |
| Release on:
February 12, 2025 | Next check:
N/A                | Released: [name]                                                                       |                  |
|                                  |                                   | Valid from: 04.09.2024                                                                                  |                  |

|                   |                          |                                                                 |  |
|-------------------|--------------------------|-----------------------------------------------------------------|--|
| study
protocol | Study: „Soziales Rezept“ | Campus:
CCM                                                  |  |
|                   |                          | Scope:
Institute for General Practice and
Family Medicine |  |

This is also done descriptively and with logistic regression or analysis of covariance with an additional factor interaction (treatment group\*subgroup) in the model. Details of the definitions of the subgroups are described in the SAP.

If there are relevant differences between the groups at baseline, these variables are additionally adjusted.

Clustering by center/physician or link worker is taken into account with different models (e.g. fixed/random effects).

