## 11 Accompanying health economic evaluation

The feasibility study is accompanied by a health economic evaluation, which uses the quantitatively collected data from the study. The aim of this is, on the one hand, to check the acceptance of the survey instruments on well-being (ICECAP-A), quality of life (EQ-5D-5L) and resource utilization (PECUNIA RUM/EHIS- GeDA ). In addition, the link worker documentation is used to extract which offers were provided to patients and how the patient -link worker interaction went. The service utilization recorded is also evaluated in a group comparison in order to identify service areas with a significant group difference. The exploratory evaluations use the 5% and 10% significance levels. The findings will be used to revise the survey instruments for a follow-up study, i.e. to delete aspects in the PECUNIA RUM instrument that are less important in the application context of “social prescription” and to include the spectrum of offers provided outside the healthcare system for standardized documentation and determination of standard costs.

In addition to the results related to this research process, the data collected on service utilization as well as on quality of life and well-being are evaluated in terms of content. For the monetary assessment of resource use, the standard costs for all (privately purchased or prescribed) services and goods are calculated in euros. The cost-effectiveness of the intervention is determined using the net benefit approach. The statistical evaluation of the data will be carried out using parametric or non-parametric methods, depending on the distribution of the data. Finally, relevant subgroups from a health economic perspective will be identified and statements will be made on the power of the results achieved in order to support the sample size estimates for a potential follow-up study.

|                                  |                                   |                                                                                                         |                 |
|----------------------------------|-----------------------------------|---------------------------------------------------------------------------------------------------------|-----------------|
| Version: V1.2                    | Last review:
February 12, 2025 | Created: [name], [name], [name], [name], [name] | Page
39of 52 |

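### Baseline adjustment is written for continuous endpoints only, so service-utilisation items measured at t0 would not routinely use their own baseline value

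*Protocol*

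**What the plan says.** Protocol section 8.4 sets the between-group analysis as "logistic regression (binary endpoints) or analysis of covariance (continuous endpoints adjusted for baseline , if available"), with centre taken into account in both. The baseline wording sits inside the parenthesis for continuous endpoints; nothing equivalent is attached to logistic regression. Section 8.5 uses the same two models for subgroups.

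Table 2 (section 3) lists "Utilization behavior of health-related services" as an endpoint at 3 and 6 months relative to baseline. Its domains run from hospital and "care facilities, emergency care, outpatient health" services to informal care and incapacity for work. The visit schedule in section 4.7 marks "utilization behavior (PECUNIA-RUM") at t0, t1 and t2, so a baseline value is collected.

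Section 11 then treats the same data separately: "The service utilization recorded is also evaluated in a group comparison", and "The exploratory evaluations use the 5% and 10% significance levels". The method is given only as: "The statistical evaluation of the data will be carried out using parametric or non-parametric methods, depending on the distribution of the data". Neither baseline nor centre appears there.

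One further sentence bears on the point, in section 8.5 under sensitivity analyses: "If there are relevant differences between the groups at baseline, these variables are additionally adjusted".

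**The concern.** A person's earlier use of a service is the natural predictor of later use. Here that value is collected and forms part of the endpoint's definition, yet the main analysis rule calls for it only when the endpoint is continuous. For the same endpoint, section 11 offers a second rule that does not mention baseline or the stratification factor (randomisation is stratified by practice, section 4.5.1). The two sections do not refer to each other, so it is unclear which governs.

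What is at stake is the efficiency of exploratory comparisons. Those comparisons do have uses: section 11 looks for service areas with a significant group difference, plans to drop less relevant parts of the resource-use instrument, and wants statements on power to support sample-size estimates for a follow-up study. Noisier comparisons make those decisions less reliable than the collected data allow.

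**Working it through.** **1. The plan's own figure.** Sections 1.6 and 8.2 give 215 randomised (143 and 72), about 30% dropout, and 150 with 6-month data (100 and 50). Check: 215 × 0.70 = 150.5; 143 × 0.70 = 100.1; 72 × 0.70 = 50.4. The figures reproduce, and 100 versus 50 is used below.

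**2. The rules side by side, for a utilisation item with a t0 value.**

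| Route | Uses t0? | Uses centre? |
|---|---|---|
| 8.4, item continuous (ANCOVA) | yes | yes |
| 8.4, item binary (logistic) | not stated | yes |
| 11, method by distribution | not stated | not stated |
| 8.5, sensitivity | only if groups differ at baseline | centre or physician clustering, by varying models |

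**3. Size for a yes/no item.** The protocol gives no rates, so every input here is an assumption. Let B be use at t0 with prevalence p, G the arm, and OR_b the odds ratio linking t0 use to follow-up use. Model: logit P(use at follow-up) = logit(p) − p·ln(OR_b) + ln(OR_b)·B + ln(0.4)·G. Two-sided 5% test, 1,500 simulated trials per setting, centre not simulated.

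| p | OR_b | Power without t0 | Power with t0 | Gain |
|---|---|---|---|---|
| 20% | 3 | 0.435 | 0.451 | 1.6 points |
| 20% | 10 | 0.355 | 0.429 | 7.4 points |
| 50% | 3 | 0.670 | 0.683 | 1.3 points |
| 50% | 10 | 0.497 | 0.597 | 10.0 points |

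With no treatment effect, both models rejected in 0.045 to 0.055 of trials. The simulation error of a single power figure is at most sqrt(0.25/1500) = 1.3 points, so the gains at OR_b = 3 mean little or no gain.

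A second set of assumptions (3,000 trials per setting, 30% use at t0) gives gains inside that range. With follow-up use of 15% or 50% by t0 use, power rises from 46% to 51% (treatment OR 0.40) and from 54% to 60% (OR 0.35). With 10% or 60% and OR 0.35, it rises from 44% to 53%.

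**4. Chance imbalance.** With 30% use at t0, the standard error of the between-arm difference at t0 is sqrt(0.3 × 0.7 × (1/100 + 1/50)) = sqrt(0.0063) = 0.079. A difference above 10 points in either direction is 0.10/0.079 = 1.26 standard errors, which occurs in about 21% of trials. Such a difference moves the unadjusted risk difference by 0.10 × (0.50 − 0.15) = 3.5 points, or by 0.10 × (0.60 − 0.10) = 5 points. Over repeated randomisations this averages to zero.

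**5. Counts.** Gamma-Poisson counts at t0 and follow-up, mean 0.5 or 2, gamma shape 0.5 or 1, rate ratio 0.6, 600 trials per setting, all assumed:

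| Method | Power range |
|---|---|
| ANCOVA on raw counts with t0 | 0.38–0.85 |
| Robust Poisson with t0 | 0.40–0.85 |
| Mann–Whitney, no t0 | 0.24–0.51 |
| Any/none logistic, no t0 | 0.19–0.32 |
| Any/none logistic with t0 | 0.24–0.35 |

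Rejection with no effect was about 0.04 to 0.07 throughout. The shortfall of the rank test mixes two things, no baseline and ranks instead of means, so it should not be credited to baseline alone. In any/none logistic regression, where only the t0 term differs, the range moves from 0.19–0.32 to 0.24–0.35.

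**The case against.** The strongest reply has four parts.

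- *Section 8.4 does not forbid a baseline term in logistic models; it is silent.* The scored scales (WHODAS 2.0, WHO-5, EQ-5D-5L and the rest) are covered by ANCOVA, and the binary comparison that 8.4 names, dropout, has no baseline value. This is fair. The gap concerns utilisation, where a t0 value exists and the endpoint is defined against it.
- *Section 8.5 already handles imbalance.* In part. Its sentence is not limited to continuous endpoints, so a reader who inferred that t0 values are ignored altogether would go too far. But it is triggered by the observed data, sits under sensitivity analyses, and does not recover the precision that a prespecified covariate gives when the arms happen to be balanced.
- *Model detail belongs in the SAP*, to which section 8.1 defers. This holds for the count model and any offset. It holds less for baseline adjustment, which 8.4 does not leave open: it states it for one endpoint type.
- *The study is exploratory and the gain is modest.* Both are true, and they limit the weight of the point.

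A reader might also infer that counts of contacts or days must be dichotomised or forced into a normal model. The protocol does not support that. Section 11 allows non-parametric methods, nothing in the protocol prescribes dichotomising, and the scale of the utilisation items is not stated. Adverse-event counts are only described, and consultation counts exist in one arm. ANCOVA on raw counts also did about as well as a count model in the check above.

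**Conclusion.** The point stands as a free improvement. As written, a utilisation item analysed as binary under section 8.4, or by a simple rank test under section 11, would not routinely use its t0 value, and section 11 does not carry over the centre adjustment of 8.4.

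For binary items at 100 versus 50 the loss is about 1 to 10 percentage points of power, depending mainly on how strongly t0 use predicts later use. The figure rests wholly on assumed prevalences and odds ratios and on a two-sided 5% test; the 10% level in section 11 was not simulated.

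It would be wrong to read this as bias or as an inflated error rate. Randomisation makes chance imbalance average out, and rejection with no effect stayed near 5% for the binary models with or without t0. Nor does it show that a particular count model is required.

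**What to change.** In section 8.4, extend the baseline clause so that every between-arm model, logistic regression included, contains the t0 value of the same item where one was collected, together with centre. In section 11, add a cross-reference so that the utilisation group comparison follows the same baseline and centre adjustment, whichever method the distribution suggests. Keep the 8.5 sentence for other variables that differ at baseline.

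The choice of model for counts can be left to the SAP. The cost is a wording change in two sections; no new data, visits or items are needed.

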### 8.5 sensitivity analyses

Relevant endpoints will additionally be analyzed using the per-protocol population.

Subgroup analyses are carried out for relevant endpoints. The following subgroups are used, among others:

- Gender
- underlying psychosocial problem(s)
- age groups.

|                                  |                                   |                                                                                                         |                  |
|----------------------------------|-----------------------------------|---------------------------------------------------------------------------------------------------------|------------------|
| Version: V1.2                    | Last review:
February 12, 2025 | Created: [name], [name], [name], [name], [name] | Page
34 of 52 |
|                                  |                                   | Reviewed by: [name], [name]                                                    |                  |
| Release on:
February 12, 2025 | Next check:
N/A                | Released: [name]                                                                       |                  |
|                                  |                                   | Valid from: 04.09.2024                                                                                  |                  |

|                   |                          |                                                                 |  |
|-------------------|--------------------------|-----------------------------------------------------------------|--|
| study
protocol | Study: „Soziales Rezept“ | Campus:
CCM                                                  |  |
|                   |                          | Scope:
Institute for General Practice and
Family Medicine |  |

This is also done descriptively and with logistic regression or analysis of covariance with an additional factor interaction (treatment group\*subgroup) in the model. Details of the definitions of the subgroups are described in the SAP.

If there are relevant differences between the groups at baseline, these variables are additionally adjusted.

Clustering by center/physician or link worker is taken into account with different models (e.g. fixed/random effects).

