##### 4.6.2 Inclusion and exclusion criteria for patients

Inclusion criteria:

- patients (18 years and older) who are capable of consenting
- Presence of one or more non-medical health-related social problems (see below)

Exclusion criteria:

|                                  |                                   |                                                                                                         |                  |
|----------------------------------|-----------------------------------|---------------------------------------------------------------------------------------------------------|------------------|
| Version: V1.2                    | Last review:
February 12, 2025 | Created: [name], [name], [name], [name], [name] | Page
23 of 52 |
|                                  |                                   | Reviewed by: [name], [name]                                                    |                  |
| Release on:
February 12, 2025 | Next check:
N/A                | Released: [name]                                                                       |                  |
|                                  |                                   | Valid from: 04.09.2024                                                                                  |                  |

|                |                          |                                                              |  |
|----------------|--------------------------|--------------------------------------------------------------|--|
| study protocol | Study: „Soziales Rezept“ | Campus:
CCM                                               |  |
|                |                          | Scope:
Institute for General Practice and Family Medicine |  |

- patients who are legally cared for in relation to health
- a person living in the same household is already included in the study

Non-medical health-related social problems are defined by chapter ZC of the International Classification of Primary Care – 3rd Revision (ICPC-3) (8) .

The classification includes problems in the following areas:

- Financial problems (including poverty)
- Problems with social benefits (including lack of receipt of social benefits, problems with incapacity to work)
- problems at work
- Unemployment as a problem
- loneliness, social isolation

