## 6.4 instruments

*Sociodemographic data:* Based on the European Health Interview and Examination Survey (EHIS) and the Diversity Minimal Item Set ( DiMiS ), sociodemographic data (e.g. age, gender, school education, occupation, gender identity and migration background) are collected (20) . In addition , the treating general practitioners record any existing long-term diagnoses of the participants.

*Health status (WHODAS 2.0):* The WHO Disability Assessment Schedule 2.0 is a generic patient-reported outcome measure of health status. The domains of WHODAS 2.0 are based on the conceptual framework of the WHO International Classification of Functioning, Disability and Health (ICF), which has been the international standard for describing and measuring health and disability since 2001. All six ICF domains (cognition, mobility, self-care, social interaction, life activities and social participation) are covered by the WHODAS 2.0 instrument. It shows high internal consistency, high test -retest reliability and high validity compared to other instruments (21,22) . A computer-based adaptive form with 12 items is available in German.

|                                  |                                   |                                                                                                         |                  |
|----------------------------------|-----------------------------------|---------------------------------------------------------------------------------------------------------|------------------|
| Version: V1.2                    | Last review:
February 12, 2025 | Created: [name], [name], [name], [name], [name] | Page
31 of 52 |
|                                  |                                   | Reviewed by: [name], [name]                                                    |                  |
| Release on:
February 12, 2025 | Next check:
N/A                | Released: [name]
Valid from: 04.09.2024                                             |                  |

|                   |                          |                                                                 |  |
|-------------------|--------------------------|-----------------------------------------------------------------|--|
| study
protocol | Study: „Soziales Rezept“ | Campus:
CCM                                                  |  |

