### 8.2 case number estimate

Since this is an exploratory feasibility study without confirmatory hypothesis testing, no formal sample size calculation will be performed. Based on previous experience, we assume that the analysis of a total of 215 participants (in a ratio of 2:1: 143 in the SP arm and 72 in the TAU+ arm) is sufficient to descriptively determine the feasibility and acceptability aspects of the study and to obtain further information for planning the subsequent study.

A drop-out of approximately 30% is expected, so that follow-up data for secondary clinical endpoints of 150 patients (n = 100 in the SP arm and n = 50 in the TAU+ arm) will be available after 6 months.

|                                  |                                   |                                                                                                         |                  |
|----------------------------------|-----------------------------------|---------------------------------------------------------------------------------------------------------|------------------|
| Version: V1.2                    | Last review:
February 12, 2025 | Created: [name], [name], [name], [name], [name] | Page
33 of 52 |
|                                  |                                   | Reviewed by: [name], [name]                                                    |                  |
| Release on:
February 12, 2025 | Next check:
N/A                | Released: [name]                                                                       |                  |
|                                  |                                   | Valid from: 04.09.2024                                                                                  |                  |

|                   |                          |                                                                 |  |
|-------------------|--------------------------|-----------------------------------------------------------------|--|
| study
protocol | Study: „Soziales Rezept“ | Campus:
CCM                                                  |  |
|                   |                          | Scope:
Institute for General Practice and
Family Medicine |  |

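### Section 8.5 tests effect modification by age with age groups; a continuous-age interaction would use the data better if modification is roughly linear

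*Protocol*

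**What the plan says.** Protocol section 8.5 plans subgroup analyses for relevant endpoints by gender, underlying psychosocial problem(s) and age groups; the list is open. The method is given in one sentence: "This is also done descriptively and with logistic regression or analysis of covariance with an additional factor interaction" of treatment group by subgroup. The next step is deferred: "Details of the definitions of the subgroups are described in the SAP". No interaction with age as a continuous variable is mentioned, and no reason for grouping is given.

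Section 6.4 says that "sociodemographic data (e.g. age, gender, school education, occupation, gender identity and migration background) are collected". It does not say whether age is held in years or in bands. Section 4.6.2 admits "patients (18 years and older) who are capable of consenting" and sets no upper age limit.

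The numbers available come from section 8.2: 215 randomised, "in a ratio of 2:1: 143 in the SP arm and 72 in the TAU+ arm", with about 30% drop-out leaving 150 with 6-month data (100 SP, 50 TAU+). The same section says that "no formal sample size calculation will be performed", and section 8.1 says all results are interpreted exploratively.

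**The concern.** Naming age groups and a factor interaction settles the form of the age analysis. What remains for the SAP is how many groups there are and where the limits fall. A factor treats everyone within a group as having the same expected treatment effect and lets it jump at the limits. If the effect in fact drifts with age, the differences within groups are thrown away, and how much is lost depends on where the cuts are placed.

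Eligible ages run from 18 upwards without a ceiling, so the potential spread is wide, and an interaction estimate from about 100 against 50 participants will be imprecise in any case. What is at stake is the efficiency of one exploratory analysis. No primary conclusion depends on it.

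**Working it through.** **The plan's own figure.** Section 8.2 gives 150 participants with 6-month data. 215 × 0.70 = 150.5; 143 × 0.70 = 100.1; 72 × 0.70 = 50.4. The figure of 150 (100 and 50) reproduces.

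**Inputs the protocol does not give, and so assumed here.** The number of age groups, the cut-points, the age distribution, and the shape of any effect modification (taken as linear).

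**Formula.** Under a linear treatment-by-age interaction, with age independent of allocation through randomisation, the share of information kept after grouping is

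retained = Var(E[age | group]) / Var(age), and loss = 1 − retained.

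**Near-normal age, equal-sized groups**
- Two groups: the group means lie at ±√(2/π) = ±0.798 SD, so retained = 2/π = 0.637 and the loss is 36%.
- Three groups: the cuts lie at ±0.431 SD and the outer means at ±3 × 0.3636 = ±1.091 SD. Retained = (2/3) × 1.091² = 0.793 and the loss is 21%.
- Four and five groups (numerically): losses of 14% and 10%.

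Applied to the 150 expected at 6 months, the effective number for the interaction is about 95 with two groups, 119 with three and 129 with four.

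**Uniform age from 18 to 90, equal-sized groups.** The loss is 1/k²: 25%, 11%, 6% and 4% for k = 2, 3, 4 and 5.

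**Sensitivity to the assumptions.** Equal-sized groups were tried on six distributions: normal; uniform 18–90; normal truncated to 18–95 with mean and SD parameters 50/17, 55/20 and 45/15; and a bimodal mixture. Fixed cuts were tried on all of these except the standard normal.

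| Grouping | Range of loss |
|---|---|
| 2 equal groups | 20–36% |
| 3 equal groups | 11–21% |
| 4 equal groups | 6–14% |
| 5 equal groups | 4–10% |
| single cut at 65 | 31–64% |
| cuts at 40 and 65 | 11–21% |
| cuts at 30, 45 and 65 | 8–13% |

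Taken together, the losses run from about 4% to about 64%.

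**Do more groups recover the test?** As an illustration only, suppose the continuous-age interaction had 80% power at a two-sided 5% level. The noncentrality is (1.960 + 0.842)² = 7.85. Multiplying by the retained share and testing on k − 1 degrees of freedom, for near-normal age and equal groups:
- k = 2: 7.85 × 0.637 = 5.0 on 1 df, power about 61%
- k = 3: 7.85 × 0.793 = 6.2 on 2 df, power about 60%
- k = 4: 7.85 × 0.860 = 6.8 on 3 df, power about 57%

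A simulation with F tests at 100:50 (2,000 data sets per setting) gave 78% for continuous age against 58%, 58% and 55%. More groups keep more information, but the extra degrees of freedom use up the gain in the test. The 80% starting point is a benchmark chosen for comparison. The protocol states no power, effect size or SD for this analysis.

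**The case against.** The strongest reply is that this is a preference about an exploratory analysis whose details belong to the SAP. Much of that stands. Section 8.1 requires the SAP before data analysis, cut-points are properly an SAP matter, and because the subgroup list is open the SAP could add a continuous-age interaction without contradicting section 8.5. Section 4.5.1 says randomisation is not done to test comparative hypotheses, so power for an age interaction is not a design criterion. The link-worker attendance endpoint exists only in the intervention arm, so no treatment interaction applies to it. Groups also have real uses: they suit the descriptive tables and do not assume linearity. What does not stand is that the protocol leaves the form open. It names groups and a factor interaction as the method.

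Four stronger readings might be inferred, and the document does not support them.
- **A definite loss, for example a fifth to a third.** That range needs near-normal age, linear modification and two or three equal groups, and none of these is stated. Even then two groups lose slightly more than a third.
- **Age is recorded as an exact value.** Section 6.4 says only that age is collected.
- **Particular power figures hold for this trial.** They need an assumed interaction slope or a benchmark such as the one used above.
- **The psychosocial-problem subgroup is mis-specified** because eligibility requires only "Presence of one or more non-medical health-related social problems" and a patient may therefore fall in several areas. Section 8.5 does not prescribe one multi-level factor. A yes/no indicator per area, each with its own interaction, already fits its wording, so the rest is SAP detail.

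**Conclusion.** The point holds as a cheap improvement with low stakes. Section 8.5 contains no error or contradiction here; it commits to a less efficient form for the age interaction without giving a reason.

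The size is conditional. With near-normal age and roughly linear modification, two equal groups lose about 36% of the information and three about 21%. More groups lose less information but gain nothing in the interaction test for the two- to four-group choices checked. An unequal split such as a single cut at 65 can lose more. Without the cut-points and the age distribution, the loss in this trial cannot be stated more closely than the range of scenarios shown. If modification by age is strongly non-linear, a linear term has no guaranteed advantage, which is why the spline check belongs in the recommendation.

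**What to change.** State in section 8.5 that the treatment-by-age interaction is estimated with age as a continuous variable, using a linear term, with a spline as a check for non-linearity, and that age groups are used for the descriptive tables. The group limits can stay in the SAP.

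The cost is about one sentence and no additional participants. It does require age to be stored at a fine enough resolution, such as years, which should be confirmed because section 6.4 does not say. The statistical downside is that a linear term can miss a non-linear pattern. The spline covers this at the price of extra degrees of freedom and with only about 50 controls expected at 6 months, so it is best read as a check on shape.
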